### Study interventions

#### Minimal screening only (MSO)

Following randomization, participants in the MSO group will receive an informational pamphlet about drug use and its consequences, addiction, and treatment. This pamphlet will consist of information collected from materials produced by NIDA for the general public. They will receive no further intervention.

#### Screening and referral (SAR)

Participants in the SAR group will receive the same informational pamphlet as the MSO group. Those with probable dependence (NM-ASSIST score ≥27 for any drug or alcohol) will also be provided with minimal scripted feedback to let them know their score is in the high-risk range, and will receive a recommendation to seek treatment. The RA will provide these participants with an information sheet listing treatment and self-help resources in their community. The latter will be standardized in format but will include site-specific information, i.e., names, addresses, and phone numbers of local addiction treatment agencies in the normal clinical referral network of the participating EDs. Based on our initial site survey, the majority of responding EDs are not currently screening or referring systematically, so the SAR condition represents a level of care significantly higher than treatment-as-usual.

#### Brief Intervention + booster (BI-B)

Individuals randomized to the BI-B condition will receive the same information and referral as those in SAR. However, in addition to these materials, while in the ED the BI-B group will receive a manual-guided BI based on motivational interviewing (MI) principles, including feedback based on screening information, the Feedback, Responsibility, Advice, Menu of options, Empathy, Self-efficacy (FRAMES) heuristic, and development of a change plan, as delivered in previous trauma center trials [6,41-44] and the Washington State SBIRT projects [6,41,42,45-49]. As Sise [50] indicated, SBIRT services such as these can be integrated effectively into all components of a busy urban ED by adding specially trained interventionists to the ED service staff and/or by training existing staff. The BI will be performed by study RAs (rather than regular ED staff members) who have received centralized training, have successfully completed and met criterion skill levels as assessed by objective ratings of tapes of their interventions with a series of subsequent training cases, and who will receive ongoing fidelity monitoring and clinical supervision over the course of the trial. For a given study participant, BI will be performed by a different RA than the one who conducted assessments of that individual. The in-person BI, which will be approximately 30 minutes long, will be delivered while the participant is still in the ED. Participants in BI-B will receive the informational pamphlet and referral for treatment (if indicated) from the BI interventionist.

In addition, as a means of augmenting the intervention in the ED, participants also will receive up to 2 phone “booster” sessions. These sessions, which are also based on MI principles, will check to see whether they have engaged in treatment, review change plans, and seek a commitment from them [51]. This number of booster sessions was chosen to replicate the structure of the standard Motivational Enhancement Therapy (MET) [52], with the goal of maximizing the magnitude of the therapeutic effect while keeping the intervention short enough to be practical. The goal of the first phone session is to re-engage and reinforce the change plan and support continuing change efforts. The second phone session is a check-in and addresses barriers to change or treatment engagement. Each of these booster calls will be approximately 20 minutes long. The content of these boosters is patterned after sessions in MET [52,53]. The phone booster process is similar to those previously used to deal with problem drinkers in EDs, either as part of stepped-care interventions initiated in the ED and continued following discharge [54] or as stand-alone phone-delivered BIs conducted without an initial intervention in the ED [51], and to procedures used in a primary care settings [55]. The target window for the initial first and second phone booster calls is within 3 days and within 7 days of discharge from the ED, respectively. If initial attempts to complete the booster sessions within these windows are unsuccessful, further attempts to engage participants will be made for up to one month post-discharge from the ED. Booster calls will be made from a centralized, study-wide intervention booster call center by interventionists who have received standardized training and will have ongoing fidelity monitoring and clinical supervision.

### Follow-up assessments

Follow-up assessments will be conducted at 3, 6, and 12 months following the ED visit. In order to maintain blinded follow-up, different RAs will be used to complete baseline and follow-up assessments. If in-person follow-up is not possible, follow-up visits may be conducted by phone, but this should be avoided if possible, as hair samples would be missing in such cases. In addition to measures of substance use (e.g., NM-ASSIST, TLFB, hair sample), the Treatment Services Review (TSR) [30] also will be administered at these follow-up points to track substance-abuse treatment entry and utilization and medical-treatment service utilization.

Follow-up will be conducted in person at a central location, preferably close to the participating ED. Additionally, if participants are unable to provide their own transportation to or from follow-up visits, sites may provide transportation including bus or taxi fare if they have local IRB approval to do so. As a means to achieve high follow-up rates in the study population, adequate compensation for time and inconvenience is critical. Compensation of $50 for the screening/baseline visit and $75 for the 3-month visit (primary outcome) and subsequent visits is proposed.

### Safety assessment

Adverse events, serious adverse events, and substance use events (e.g., worsening of drug use, need for higher level of care, admission to detox or inpatient drug treatment) will be monitored and reported throughout the study. These events will be subject to ongoing monitoring by the study executive committee and will be presented for review by the independent Data and Safety Monitoring Board.

### Blinding

As in almost all psychosocial treatment protocols, study participants will not be blinded. However, because of the two-stage method of revealing the randomized group assignments, RAs conducting baseline assessments will be partially blinded until the assessment has been completed. The RAs conducting follow-up assessments will be different from those conducting the baseline assessments and will be blinded to treatment condition. To further minimize potential bias, the RA who conducts the baseline assessment in the ED will not be the same one that conducts the BI-B intervention with that patient.

### Sample size determination

There is no straightforward way to estimate the effect size of the proposed contrasts across the three conditions due to differences across critical aspects of prior SBIRT studies (e.g., primary care setting rather than ED, or alcohol versus drug use as the primary outcome). While previously published studies guided our estimates of treatment effect, the power analysis and sample size calculations were based on the minimum clinically significant nonstandardized effect that we wish to be able to detect between SAR and BI-B, and estimates of error variance based on the data collected in the Washington State implementation of an SBIRT model in ED setting [48,56]. In order to detect an absolute difference of three days between the two groups, which was considered to be a clinically meaningful difference, and with an estimated standard deviation of 11 days, an anticipated 15% attrition rate, and a Type I error *α* = .05/3 (two-tailed), a total of 1285 subjects (429 in each arm) was determined necessary to have 90% power. Estimating conservatively that 5% of screened patients will meet inclusion criteria, and that 75% of these will consent to participate in the study, it will be necessary to screen 34,267 patients (5711 per site) to achieve the proposed sample of 1285 randomized participants. We propose to screen approximately 160 individuals per week per site to achieve the targeted enrollment rate of six participants per week per site. This will allow recruitment at each site to be accomplished within nine months.

### Statistical methods for primary analyses

The primary analyses will consist of three prespecified pair-wise comparisons between the MSO, SAR, and BI-B conditions with respect to the primary outcome variable (number of days of use of the primary drug of abuse in the past 30 days at three-month follow-up based on the TLFB), all of which will use a simple closed testing procedure to control family-wide Type I error at no more than 0.05. Linear mixed-model analyses with a random site effect and fixed treatment effect and intercept will be used. These analyses will take into account possible variability in the overall level of abstinence between the sites, possible site-by-treatment interaction, and the level of a baseline covariate (days of use of the primary drug of abuse, as defined at screening by the DAST-10, during the 30 days preceding the baseline assessment). The primary outcome will be analyzed according to the intent-to-treat principle. Patients who refuse treatment will still be followed for outcome in their assigned group, but no attempt will be made to impute outcomes for these patients.

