### Primary hypotheses

There are three primary hypotheses: (1) Participants randomized to BI-B will have fewer days of use of the patient-defined primary problem substance during the 30 days prior to the 3-month assessment relative to participants randomized to MSO; (2) participants randomized to BI-B will have fewer days of use relative to participants randomized to SAR; and (3) participants randomized to SAR will have fewer days of use relative to participants randomized to MSO.

The study also has a number of secondary objectives: (1) To evaluate the effect of BI-B relative to SAR on substance abuse treatment engagement among those participants who are referred to treatment; (2) to evaluate the effect of the experimental interventions on self-reported health-care utilization; (3) to evaluate several putative predictors of outcome (patient demographics, substance use severity at baseline, primary substance of abuse, motivation, therapeutic alliance, perceived substance-relatedness of ED visit, and psychiatric comorbidity) in terms of both main effect and interaction with treatment assignment; and (4) among participants assigned to BI-B, to evaluate dose–response to the number of booster sessions received.

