### Randomization procedure

After providing informed consent, all eligible participants will be randomly assigned in 1:1:1 ratio to one of the three conditions (MSO, SAR, or BI-B). Randomization will be stratified based on site, presence of an alcohol use disorder (AUDIT-C score ≥ 4), and drug problem severity (DAST-10 score ≥ 8). The randomization procedure will be conducted through a centralized, web-based process set up by the NIDA Clinical Trials Network Data and Statistics Center. The randomization sequence will be unknown to staff, and treatment assignment will be revealed in two stages. Initially, the RA performing the randomization will be informed as to whether the participant is in the MSO group or not. If so, the RA is finished with the research component in the ED and will have no further study involvement until the 3-month follow-up visit. The remaining participants will receive a more extensive baseline assessment. After completion of the baseline assessment, RAs will be informed whether participants are in the SAR or BI-B group. Research assistants conducting the follow-up assessments will be blinded to treatment condition. The randomization scheme was designed to balance patient allocation to each treatment arm. Given the intent-to-treat nature of the study, participant dropouts after randomization will not be replaced.

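### Two of the three stratification factors, AUDIT-C ≥ 4 and DAST-10 ≥ 8, are absent from the stated primary model; if they are prognostic, its tests are slightly conservative

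*Protocol article*

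**What the plan says.** Under Randomization procedure, participants are "randomly assigned in 1:1:1 ratio to one of the three conditions", and the allocation is "stratified based on site, presence of an alcohol use disorder (AUDIT-C score ≥ 4), and drug problem severity (DAST-10 score ≥ 8").

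Under Statistical methods for primary analyses, the model is "Linear mixed-model analyses with a random site effect and fixed treatment effect and intercept will be used". The next sentence says that the analyses allow for between-site variability in the outcome, "possible site-by-treatment interaction, and the level of a baseline covariate (days of use of the primary drug of abuse"). No term for the AUDIT-C or the DAST-10 stratum is named. The DAST-10 does appear in that sentence, but only to say how the primary drug is identified at screening; that does not bring the severity stratum into the model.

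Under Primary hypotheses, a secondary objective lists "putative predictors of outcome (patient demographics, substance use severity at baseline" among several factors to be examined.

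**The concern.** Stratified allocation balances the arms on the stratification factors, so those factors contribute little to the real sampling variation of the difference between arms. If they predict the outcome and are left out of the model, their variance stays in the residual. The reported standard error then overstates the real one, confidence intervals are too wide, and the test rejects less often than its nominal level.

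The direction matters here because the article draws conclusions from null results. Its Table 1 reads equality between arms as absence of assessment reactivity or of a treatment effect, and the accompanying text argues against using an intervention that does not add significantly to assessment and referral. Conservative tests lean toward those readings. All three primary contrasts use the same model.

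**Working it through.** **Inputs from the protocol article (Sample size determination).** The target is stated as "In order to detect an absolute difference of three days between the two groups", "with an estimated standard deviation of 11 days" and "an anticipated 15% attrition rate". Alpha is 0.05/3 = 0.01667 two-sided, power is 90%, and the sample is 429 per arm, 1285 in total. No reduction of the SD for any covariate is stated.

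**Assumption.** The article does not give the share of residual variance that the two strata explain, given site and baseline days of use (partial R²). The range taken is 0 to 0.10. Zero belongs in it, because nothing in the article rules it out.

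**Step 1: reproduce the plan's figure.** n per arm = 2 × [11 × (2.394 + 1.282)/3]² = 363.3, rounded up to 364. Allowing for attrition, 364/0.85 = 428.2, so 429 per arm; 3 × 364/0.85 = 1284.7, so 1285. Both stated figures reproduce. With 429 × 0.85 = 364.65 evaluable per arm, SE = 11 × √(2/364.65) = 0.815 days and power is 90.1%.

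**Step 2: effect of the omitted strata.** With the strata in the model, SE = 0.8146 × √(1 − R²). Without them, the reported SE stays at 0.8146, which is too wide by the factor 1/√(1 − R²). The equivalent number of completers in a two-arm contrast is 2 × 364 × R² = 728 × R². Power with the strata is Φ(3/SE − 2.394). Power without them, under stratified allocation, is Φ[(3 − 2.394 × 0.8146)/SE], because the estimate really varies with the smaller SE but is tested against the larger one. Actual size without them is 2 × [1 − Φ(2.394/√(1 − R²))].

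| Partial R² (assumed) | SE with strata (days) | Reported SE too wide by | Completers equivalent, of 728 | Actual size without strata (nominal 1.67%) | Power without strata | Power with strata |
|---|---|---|---|---|---|---|
| 0 | 0.815 | 0% | 0 | 1.67% | 90.1% | 90.1% |
| 0.02 | 0.806 | 1.0% | 15 | 1.56% | 90.4% | 90.8% |
| 0.05 | 0.794 | 2.6% | 36 | 1.40% | 90.7% | 91.7% |
| 0.10 | 0.773 | 5.4% | 73 | 1.16% | 91.3% | 93.2% |

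Against the planned 90.1%, adjusted power is 0 to 3 points higher. Against the same trial analysed without the strata, the gain is smaller, 0 to 1.9 points.

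**Step 3: simulation check.** There were 3,000 replicates per scenario, with 730 evaluable participants in two arms, 6 × 2 × 2 strata, permuted blocks, an assumed baseline–outcome correlation of 0.4, and site as a fixed effect. Site and baseline days of use were in both models.

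- At partial R² 0.05, the model without strata gave a mean reported SE of 0.747 against an empirical SD of 0.733, and null rejection of 1.27%. Power was 95.4% without and 95.9% with the strata.
- At partial R² 0.10, the reported SE was 0.747 against 0.712, and null rejection was 1.2%. Power was 95.3% without and 96.5% with the strata.
- At partial R² 0, the two models did not differ materially.

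The Monte Carlo standard error of a rejection rate near 1.67% is √(0.01667 × 0.98333/3000) = 0.23 points. The simulated sizes therefore agree with the formula but are not precise on their own. At partial R² 0.02, where the simulated rate was 1.9%, the effect is too small for this number of replicates to show.

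**The case against.** The strongest objection is that this is a condensed design article. It describes the model in two sentences and does not say that the list is complete, so the full analysis plan may already hold the stratum terms. That possibility is real. But the article chose to name its model terms and its single baseline covariate, and those do not match its own randomization. The mismatch is in what is written, not in what is left out.

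The second objection is that the loss is conditional, and this stands in full. Baseline severity is called only a putative predictor, to be evaluated. Nothing says that an alcohol screen predicts days of use of another drug. The planned covariate is the baseline counterpart of the outcome and may already carry much of the severity signal.

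The third objection is that no promised property fails, and this stands too. The sample size was set at an SD of 11 with no covariate reduction, so the 90% power does not depend on these terms.

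A reader might infer that the primary standard errors are definitely too wide, that the trial is short of power, or that as many as 109 of 1,092 completers (1285 × 0.85) are thrown away. The documents support none of these. The first depends on an unknown R². The second is contradicted by the reproduced 90.1%. The third counts three arms where each contrast uses two, and what is forgone is precision beyond the target. Nor is there a stated model for secondary outcomes to criticise.

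**Conclusion.** The point holds as a minor mismatch between design and analysis. That the two stratum terms are absent from the stated model is plain from the text, and the direction (conservative, unbiased, no excess false positives) follows from stratified allocation and is supported by the simulation. The size is unknown. It is nil if the strata add nothing beyond site and baseline days of use, and it reaches a 5.4% excess in the standard error, about 73 of 728 completers, only at the top of an assumed range. This is an efficiency improvement worth making, not a flaw that endangers the primary conclusions.

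**What to change.** Add AUDIT-C ≥ 4 and DAST-10 ≥ 8, coded as used in the randomization system, as fixed effects in the primary model beside site, treatment and baseline days of use. If the full analysis plan already contains them, correct the stated model to say so.

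The cost is one line in the model statement and two indicator parameters. Both scores come from the screening questionnaire completed before randomization, so they exist for every participant, including the minimal-screening-only arm, which has no extended baseline assessment. No new data are needed and the sample size does not change. The terms should be fixed before outcome data are seen by arm.

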### Primary and secondary outcome measures

The primary outcome for the study is the number of days of use of the patient-defined primary problem drug, assessed for the 30-day period preceding the 3-month post-intervention follow-up, as assessed by the Timeline Followback (TLFB) [27,28].

In addition, a number of secondary outcomes are included: (1) number of days of primary problem substance use during the 30 days preceding the 6- and 12-month postintervention follow-ups; (2) days of abstinence from all drug use during the 30 days preceding the 3-, 6-, and 12-month postintervention follow-ups; (3) days of heavy drinking in the past 30 days at 3, 6, and 12 months; (4) quantity of use (dollar value, number of times used) for the primary drug at 3, 6, and 12 months from baseline; (5) change in days of use of the primary drug between baseline and follow-up at 3, 6, and 12 months (only for the SAR and BI-B groups that completed the TLFB at baseline); (5) relative change in hair-sample drug screen results for the primary drug and also for any drug of abuse from baseline to 3, 6, and 12 months postintervention; (6) consequences of drug use (based on the NIDA-Modified Alcohol, Smoking and Substance Involvement Screening Test (NM-ASSIST) [29]; (7) participation in addiction treatment in the past 30 days at 3, 6, and 12 months postintervention among SAR and BI-B participants with probable dependence who are referred for treatment (assessed with the Treatment Services Review [TSR]) [30]; and (8) health-care utilization (number of ED visits, number of hospital days, and number of outpatient visits) in the past 30 days at 3, 6, and 12 months based on TSR results.

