The logistics of conducting screening in the ED require that the screening process be relatively brief and minimally intrusive. Further, to minimize potential assessment reactivity in the MSO group, substance-related screening questions were to be kept at an absolute minimum. A four-section screening instrument, the Tobacco, Alcohol, and Drug (TAD) questionnaire, will be used to capture the substances assessed. To maximize confidentiality, the TAD will be completed by the participants, who will enter the data directly using the tablet PC unless the participant is not comfortable with this technology, in which case the data may be entered by the RA. The four sections, which can be completed in 5–10 minutes, consist of (1) the 4-item Heavy Smoking Index [31], a brief screen for nicotine dependence that is administered first to minimize participant discomfort with answering more sensitive questions about drug use; (2) the three consumption items of the Alcohol Use Disorders Identification Test (AUDIT-C) [32,33]; (3) the DAST-10 [34-36]; and (4), for individuals scoring ≥3 on the DAST-10, three questions to determine primary substance of abuse, days of use of the primary substance, and substance-relatedness of the ED visit. The screen is considered positive if the DAST-10 score is ≥ 3 *and* the individual reports past 30-day use of the primary substance.

Participants who meet screening criteria based on the TAD will be further screened for eligibility by the RA, who will ask participants about (1) current engagement in addiction treatment, (2) whether they reside more than 50 miles from the follow-up location, (3) ability to provide at least two locators, and (4) access to a phone. These two prescreening forms (the TAD and eligibility) will not include identifying information. Individuals who are interested and eligible to participate will then undergo the informed consent process. Patients who do not meet inclusion criteria will receive no further intervention, but the anonymous screening data will be kept to allow comparison to those who do meet criteria.

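### The primary model does not adjust for which drug each patient's outcome counts, although this is recorded in every arm before randomization; adding it could give a small gain in precision at almost no cost.

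*Protocol article*

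**What the plan says.** All references are to the protocol article.

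- **Outcome** (Primary and secondary outcome measures): "number of days of use of the patient-defined primary problem drug, assessed for the 30-day period preceding the 3-month post-intervention follow-up", taken from the Timeline Followback. Patients with different primary drugs are therefore analysed together on one 0 to 30 day scale.
- **Model** (Statistical methods for primary analyses): random site, fixed treatment and an intercept, with allowance for a possible site-by-treatment interaction and for "the level of a baseline covariate (days of use of the primary drug of abuse", the drug being the one identified at screening. No other patient-level covariate is named.
- **Availability of the drug** (Screening of potential participants): patients scoring 3 or more on the DAST-10 answer "three questions to determine primary substance of abuse, days of use of the primary substance, and substance-relatedness of the ED visit". Screening precedes consent and consent precedes randomization, so the answer exists for MSO, SAR and BI-B alike.
- **Expected relevance** (Primary hypotheses): a secondary objective is "to evaluate several putative predictors of outcome (patient demographics, substance use severity at baseline, primary substance of abuse" and several others, each as a main effect and as an interaction with treatment.
- **Stratification** (Randomization procedure): "Randomization will be stratified based on site, presence of an alcohol use disorder" (AUDIT-C of 4 or more) and drug problem severity (DAST-10 of 8 or more). Primary drug is not a stratum.

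**The concern.** Primary drug is not an ordinary optional covariate here, because it defines what each patient's outcome counts. Typical days of use, and the change in days over three months from the same starting level, may differ between drugs. If they do, part of the outcome variance belongs to drug class. The stated model puts that part in the residual unless baseline days already captures it.

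What is at stake is precision in the three primary contrasts (BI-B vs MSO, BI-B vs SAR, SAR vs MSO). The information needed is already collected in every arm, and the article itself considers the variable a plausible predictor.

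**Working it through.** **Inputs from Sample size determination.** Difference of 3 days ("In order to detect an absolute difference of three days between the two groups", SAR and BI-B); SD and attrition "with an estimated standard deviation of 11 days, an anticipated 15% attrition rate"; two-sided alpha .05/3 = 0.0167; power 90%; 1285 patients in total, 429 per arm.

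**Input not in the article.** The partial R-squared of drug class, given site and baseline days. The article gives no drug mix, no mean days by drug and no variance explained. I assume a range of 0% to 10%.

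**Step 1: reproduce the plan's figure.**
n per arm = 2 (z for 1 − .05/6 + z for .90)² (11/3)² = 363.3, rounded up to 364 evaluable. 364/0.85 = 428.2, rounded up to 429 per arm. 3 × 429 = 1287, against the stated 1285. The figure reproduces to within 2 patients, with no adjustment for drug class.

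**Step 2: standard error and power as planned.**
Evaluable per arm = 429 × 0.85 = 364.65.
SE = 11 × √(2/364.65) = 0.815 days.
Normal-approximation power for 3 days = 90.1%.

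**Step 3: add drug class.**
Residual SD = 11 × √(1 − R²), put into the same formulas.

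| Assumed partial R² | Residual SD | SE (days) | Fall in SE | Power for 3 days |
|---|---|---|---|---|
| 0% | 11.00 | 0.815 | 0% | 90.1% |
| 2% | 10.89 | 0.806 | about 1% | 90.8% |
| 5% | 10.72 | 0.794 | about 2.5% | 91.7% |
| 10% | 10.44 | 0.773 | about 5% | 93.2% |

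**Step 4: sensitivity to what the SD of 11 means.**
The article does not say whether 11 days is a raw SD or one already adjusted for baseline. If it is raw, and baseline days correlates 0.5 with outcome (an assumption), the residual SD before adding drug class is 11 × √(1 − 0.25) = 9.53. Power is then already 96.8%. At a partial R² of 2% it becomes 97.1%, and at 10% it becomes 98.2%. The proportional fall in SE is unchanged, but the gain in power is smaller.

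**The case against.** The strongest reply is that nothing is wrong. The model is prespecified and adjusts for the baseline value of the outcome variable. In a randomized trial, omitting a further prognostic variable from a linear model does not bias the contrasts, and the planned power is met without it. All of that stands.

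A second reply is that baseline days already absorbs the effect, since daily against episodic use is largely what that covariate measures. This stands in part, and it is why the range must start at 0%. Absorption need not be complete. The full Timeline Followback is done at baseline only in SAR and BI-B, so the baseline-days value available in all arms is a single screening item, and error in it would leave some between-drug difference behind. How much is unknown.

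A third reply is that primary drug is only one of several putative predictors to be evaluated under a secondary objective, and that an analysis plan not shown may extend the covariate list. Listing it there does not establish that it predicts outcome. But the article is not silent on covariates: it names one, and the variable that defines the outcome is the natural next candidate.

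A reader might infer that drug class is wholly uncontrolled, or that a chance imbalance in drug mix is a further harm. Neither follows. Randomization balances drug mix in expectation, and baseline days captures part of any effect. Chance imbalance is already contained in the unadjusted SE of 0.815 days, so counting it separately would count the same loss of precision twice.

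**Conclusion.** The point holds as a conditional, low-cost gain in efficiency. The stated model omits a variable that defines each patient's outcome, is known before randomization in every arm, and is named by the article as a possible predictor. The benefit depends entirely on an assumed partial R-squared. At 0% there is none; at 2% to 10% the SE of each contrast falls by about 1% to 5%, and power for 3 days moves from about 90% to between 91% and 93%.

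It would go too far to say that the three contrasts certainly carry avoidable noise, that they are biased, or that the trial is underpowered. The article supplies no variance figure for the first, randomization rules out the second, and the reproduced sample size contradicts the third.

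**What to change.** In Statistical methods for primary analyses, add one sentence naming primary drug class, as recorded by the screening question, as a fixed categorical covariate in the primary model. State the rule for pooling sparse classes in advance, based on counts over all arms combined and set blind to treatment arm. Keep the site and treatment terms, the baseline-days covariate and the closed testing procedure as planned.

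The cost is a few degrees of freedom (4 if there are five classes) out of about 3 × 364 = 1,092 observations, plus the work of fixing the pooling rule. No new data are needed. Letting the baseline-days slope differ by class is optional; its benefit has not been quantified and it is not part of this recommendation.
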